## **Statistical Analyses**

### ***Primary Outcome***

This analysis will follow the intention-to-treat principal, such that all randomized participants will be included to estimate treatment effects, irrespective of deviations from treatment protocol (e.g., loss to follow-up, non-compliance). This will be done using linear mixed models using maximum likelihood estimation. The model will include random intercepts and slopes, and fixed effects of time (baseline, month 6, month 12), treatment assignment (CON, EX, Cog-Plus), and their interaction. Baseline MMSE and ADAS-Cog-Plus scores will also be included as fixed effect covariates. Time will be specified as a categorical variable, thus allowing us to examine treatment differences at the primary endpoint (month 6) and then, as a secondary objective, whether those differences persist at the 6-month follow-up (month 12). Two planned simple contrasts will be performed using the Dunnett test. These contrasts will be employed to assess differences between: 1) the EX group and the CON group; and 2) the Cog-Plus group and the CON group. The overall alpha will be set at 0.05. A secondary complete-case analysis will be conducted using this linear mixed model, in which participants with valid data at all time points will be included. As an exploratory strategy, multiple imputation will be used to judge the impact of missingness on the conclusions drawn from this study.

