### **Sample Size Calculation**

We have designed our trial to allow the evaluation of statistical significance of the treatment effect between groups on the ADAS-Cog-Plus. A number of pharmaceutical RCTs in vascular dementia – a population highly relevant to our proposed study – have shown positive cognitive effects as measured by the ADAS-Cog, and it has been suggested that the ADAS-Cog-Plus shows greater sensitivity to underlying changes in cognition. A previous RCT of physical activity in older adults at risk for Alzheimer's disease with ADAS-Cog as the primary outcome measure demonstrated a standardized effect size of 0.60^17. We used interim results from our PROMOTE study – an exercise RCT in adults with mild sub-cortical ischaemic vascular cognitive impairment – for our sample size estimation. Based on data collected from 15 participants who have completed the RCT, we found the mean change in the ADAS-Cog score was 2.7 (SD=2.3) and 0.87 (SD=3.4) for the exercise training group and the control group, respectively. The minimally clinically relevant change (MCRC) on the ADAS-Cog varies between 3 and 5 points, with a change of  $\geq 4$  being recommended by the Food and Drug Administration. Recently, Schrag and colleagues established the MCRC empirically using data collected from the Alzheimer's disease Neuroimaging Initiative. They found that a 3-point change on the ADAS-Cog is an appropriate MCRC. Assuming a mean change of 3 points on the ADAS-Cog for both the EX and Cog-Plus groups and a mean change of 1 point for the CON group at 6 months, a common standard deviation of 2.85, and an alpha of 0.05, 39

participants per group (i.e., total sample of 117) will provide a power greater than 0.80^79. We then assumed a standardized effect size of 0.7 for the ADAS-Cog-Plus, as it has greater sensitivity to changes in cognitive function compared with the 11- or 13-item ADAS-Cog. After accounting for 15% attrition and 2:2:3 allocation, 34 participants were randomized to the EX group, 34 to the ENRICH group, and 52 to the BAT group, for a total sample of 120.

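### The primary mixed model is specified with maximum likelihood, which makes standard errors about 2% too small; restricted maximum likelihood with Kenward-Roger inference is a minor, free improvement

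*Protocol*

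**What the plan says.** The protocol's Statistical Analyses section, under Primary Outcome, fixes these points:

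- Estimator: "This will be done using linear mixed models using maximum likelihood estimation".
- Random part: "The model will include random intercepts and slopes".
- Fixed part: "fixed effects of time (baseline, month 6, month 12), treatment assignment (CON, EX, Cog-Plus), and their interaction", and in addition "Baseline MMSE and ADAS-Cog-Plus scores will also be included as fixed effect covariates".
- Inference: "Two planned simple contrasts will be performed using the Dunnett test", each comparing an active arm with CON, and "The overall alpha will be set at 0.05".

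The section does not state sidedness, degrees of freedom or the reference distribution. A protocol may leave these to the SAP, and their absence is not criticised here. No likelihood-ratio comparison of models with different fixed effects is planned.

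The Sample Size Calculation section gives the numbers: "After accounting for 15% attrition and 2:2:3 allocation, 34 participants were randomized to the EX group, 34 to the ENRICH group, and 52" to the third arm. I read ENRICH as Cog-Plus and the third arm as CON.

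**The concern.** ML estimates variance components as if the fixed effects were known. In the simplest case it divides the residual sum of squares by n, where an unbiased estimate divides by n minus the number of mean parameters. The bias always runs the same way: standard errors too small, intervals too narrow, and a test that rejects slightly too often. The two primary contrasts are the only comparisons with allocated alpha, so they are where this matters.

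Full ML is needed when models with different fixed effects are compared by likelihood ratio. The plan has no such comparison, so it accepts the bias and gains nothing from it. The complete-case analysis is to use the same model and would inherit the bias.

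**Working it through.** **1. The plan's own figure.** The protocol gives no error rate under ML, so only its sample size can be reproduced. Its premise is "Assuming a mean change of 3 points on the ADAS-Cog for both the EX and Cog-Plus groups and a mean change of 1 point" for CON, a difference of 2 points, with SD 2.85, so d = 2/2.85 = 0.702. With the two-sided 0.05 split over two contrasts (0.025 each), n = 2(2.241 + 0.842)²/0.702² = 38.6, or 39 per arm, with power 0.804. This matches the stated 39 per group and power above 0.80. It also fits a two-sided test with two comparisons, which I assume below.

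**2. Inputs.**
- Randomized: 34 + 34 + 52 = 120.
- After 15% attrition: 0.85 × 34 = 28.9 and 0.85 × 52 = 44.2, about 29/29/44 = 102.
- Fixed effects: 3 × 3 = 9 time-by-arm means plus 2 covariates = 11. About five bear on the month-6 contrast (three arm means and two covariates), so p = 5.

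**3. Standard errors.** With complete data, and month-6 scores analysed with baseline as a covariate, the ratio of ML to REML standard errors is √((n − p)/n).
- n = 120: √(115/120) = 0.979, or 2.1% too small.
- n = 102: √(97/102) = 0.975, or 2.5% too small.
- Counting only the three arm means at n = 102: √(99/102) = 0.985, or 1.5% too small.

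With p = 5, a nominal 95% interval for a single contrast covers about 94.5% (n = 120) or 94.4% (n = 102).

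**4. Two-contrast error rate.** The contrasts share CON, so their correlation is n_active/(n_active + n_CON): 34/86 = 0.395 or 29/73 = 0.397. The error rate is the probability that the larger |T| of a bivariate t with n − 5 degrees of freedom exceeds the Dunnett critical value times the ratio from step 3.

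| n | Dunnett t value | Effective cut-off under ML | Error, ML | Error, REML |
|---|---|---|---|---|
| 120 | 2.250 | 0.979 × 2.250 = 2.203 | 0.056 | 0.050 |
| 102 | 2.255 | 0.975 × 2.255 = 2.199 | 0.057 | 0.050 |

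**5. Check in a mixed model with dropout.** The simulation used a random intercept and slope, 34/34/52 participants, 10% lost before month 6 and 5% more before month 12, assumed variances and post-baseline scores only as the response (758 runs). Mean standard errors were 0.1126 (ML) and 0.1152 (REML), a ratio of 0.977. At a critical value of 2.25 the error was 0.059 (ML) and 0.051 (REML). With a Monte Carlo error of about 0.009, these rates agree with step 4 but would not establish it alone.

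**6. The model as literally written.** Baseline ADAS-Cog-Plus appears both as the first response level and as a covariate. In a small simulation of that model (154 runs, assumed variances, Monte Carlo error about 0.026), the ratio of standard errors was again about 0.0885/0.0905 = 0.978. The two-contrast error was about 0.12 under ML and 0.10 to 0.12 under REML.

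**The case against.** The strongest reply is that this is a preference and not an error. ML is a valid and common likelihood method for incomplete repeated measures. It lets all randomized participants contribute, and the protocol nowhere claims that it gives exactly 0.05. The excess is 0.6 to 0.7 percentage points in a proof-of-concept trial meant to inform a larger one. All of this stands, and it sets the weight of the point. It does not supply a reason to prefer ML here, since REML uses the same data under the same missing-data assumption.

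Three stronger readings are tempting, and the document does not support them.

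- A reader might infer that ML raises the error rate to about 6.2%. That figure (0.060 to 0.062) needs a large-sample critical value of about 2.22, which the protocol never specifies. REML with that same value still gives 0.053 to 0.054, so part of the excess comes from the critical value.
- A reader might infer that the secondary intervals are equally affected. The section on secondary and tertiary outcomes names linear mixed models but no estimator, and allocates no alpha.
- A reader might infer that changing to REML restores 0.05. The 0.050 in step 4 holds for the ANCOVA-type analysis. Step 6 suggests that the double use of baseline matters more and that REML leaves it in place.

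**Conclusion.** The point holds as a minor improvement. Under ML, the standard errors of the primary contrasts are about 2% too small (2.1% at n = 120, 2.5% at n = 102), and the two-contrast Dunnett error is about 0.056 to 0.057 instead of 0.05. The error rates rest on four assumptions: a two-sided test, a t-based critical value, about five parameters bearing on the month-6 contrast, and baseline used only as a covariate. The ratio of standard errors barely changes when baseline is also a response, but the error rate does. This is not a failure of error control, and no design decision turns on it.

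**What to change.** In the Primary Outcome analysis, replace maximum likelihood estimation by restricted maximum likelihood with Kenward-Roger standard errors and degrees of freedom, and state that the Dunnett critical value is taken from those degrees of freedom. The complete-case analysis follows automatically because it uses the same model.

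The cost is one line of wording and a software option. Intervals widen by about 2.2% (1/0.979) to 2.5% (1/0.975). The sample size, data collection and missing-data assumption stay as they are. Nothing planned is lost, because no likelihood-ratio comparison of fixed effects is foreseen.

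The double role of baseline ADAS-Cog-Plus needs its own correction. Until that is made, the amended text should not say that the change of estimator secures an overall 0.05.

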### ***Measurement***

There will be three primary measurement sessions: baseline, 6 months, and 12 months. Baseline measurements will be obtained prior to randomization. Additional secondary measures will be assessed monthly by unblinded assessors throughout the 12-month study. Data will be entered and scored using standard scoring procedures for each measure. Paper files will be held in secure filing cabinets and digital data will be stored on encrypted hard drives in laboratory areas with limited, key card access. All participant materials will be identified by identification number to maintain participant confidentiality.

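### Random slopes on three-visit categorical time, with baseline ADAS-Cog-Plus as both response and covariate, leave the primary model either degenerate or with month-6 standard errors that are too small

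*Protocol*

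**What the plan says.** All of the following is in the protocol, under Statistical Analyses, Primary Outcome, unless noted.

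- Estimation: "This will be done using linear mixed models using maximum likelihood estimation".
- Structure: "The model will include random intercepts and slopes, and fixed effects of time (baseline, month 6, month 12"), plus treatment and the treatment-by-time interaction.
- Coding of time: "Time will be specified as a categorical variable".
- Covariates: "Baseline MMSE and ADAS-Cog-Plus scores will also be included as fixed effect covariates".
- Target: "treatment differences at the primary endpoint (month 6"), with month 12 as a secondary objective.
- Error control: "Two planned simple contrasts will be performed using the Dunnett test", each active arm against CON, and "The overall alpha will be set at 0.05".
- Visits, under Measurement: "There will be three primary measurement sessions: baseline, 6 months, and 12 months".

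The protocol does not say whether the random slope is on numeric time or on the time categories. It also does not say whether the month-6 contrast is the arm difference at month 6 (level) or the arm difference in change from baseline (change).

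**The concern.** Two choices in the same paragraph interact. Three visits give little room for random intercepts and slopes plus a residual. In addition, the baseline score sits on both sides of the equation: it is a response value and also a predictor of that same value. The fit can then drive the baseline residual towards zero, and the covariance structure has to absorb the consequence.

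At stake are the two Dunnett contrasts at month 6, the only comparisons to which alpha is allocated. If the fit fails, a structure has to be chosen after the data are seen. If it runs with a linear slope, the standard errors are likely to be too small and the tests too liberal.

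**Working it through.** The protocol gives no figure for this model, so there is none to reproduce. Its sample-size figures do not depend on this point.

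**Inputs.** From the protocol: three visits, ML, arms of 34/34/52, two comparisons with CON, alpha 0.05. Assumed: two-sided testing; unit variance; compound symmetry or AR(1) between visits; visits at t = 0, 1, 2.

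**1. Slopes on categorical time.** An intercept and two time-category effects per person give 3 × 4 / 2 = 6 variances and covariances. With the residual variance that is 7 parameters. A 3 × 3 covariance matrix has 6 distinct elements, and the Jacobian has rank 6. With compound symmetry 0.8, residual variances of 0.01, 0.10 and 0.19 all reproduce exactly the same marginal covariance.

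**2. The same reading with baseline also a covariate.** Let b be the covariate coefficient. The baseline residual is (1 − b)Y0, and the residual covariance R has determinant (1 − b)² × |S|. Under compound symmetry 0.8, |S| = 0.2² × 2.6 = 0.104. The profiled −2logL per participant (constant omitted) is 2 ln(1 − b) + ln 0.104 + 3:

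| b | −2logL per participant |
|---|---|
| 0.9 | −3.9 |
| 0.99 | −8.5 |
| 0.999 | −13.1 |
| 0.9999 | −17.7 |

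It falls without limit as b approaches 1, so there is no ML solution.

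**3. Linear slope.** This has 3 + 1 = 4 parameters for 6 elements and can be fitted. It imposes V6 = (V0 + V12)/2 − var(slope). Take compound symmetry 0.8 and b = 0.9 as an illustration:

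- The baseline residual variance is (1 − 0.9)² = 0.01.
- At months 6 and 12 it is 1 + 0.81 − 2 × 0.9 × 0.8 = 0.37.
- If the model matched the two end visits, V6 could be at most (0.01 + 0.37)/2 = 0.19, against 0.37 needed.

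The actual fit compromises, but the month-6 variance is still understated.

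**4. Size in large samples.** The best-fitting ML linear-slope model, with baseline in both roles, was found for compound symmetry and AR(1) with correlation 0.5-0.9. Model SE over true SE at month 6:

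- level: 0.74-0.83
- change: 0.87-0.91

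With a random intercept only and baseline still duplicated, the change ratio is 1.00 under compound symmetry and 1.08-1.14 under AR(1); the level ratio is 0.82-0.98.

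**5. Simulated two-contrast error rate.** 1,000 runs each, 34/34/52, complete data, no treatment effect, Dunnett critical z = 2.222. The Monte Carlo SE at 5% is √(0.05 × 0.95/1000) = 0.007.

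| Model fitted; true covariance (correlation 0.8) | Level | Change |
|---|---|---|
| Linear slope, baseline twice; compound symmetry | 0.176 | 0.092 |
| Linear slope, baseline twice; AR(1) | 0.124 | 0.083 |
| Random intercept only, baseline twice; compound symmetry | 0.113 | 0.054 |
| Linear slope, baseline response only; compound symmetry | 0.052 | 0.059 |
| Linear slope, baseline response only; AR(1) | 0.057 | 0.054 |

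The duplicated baseline harms the level contrast with or without the slope. In the change contrast, inflation appears when the slope is added to the duplicated baseline.

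**6. Baseline as response only, linear slope kept.** The change-contrast SE ratio is 1.00 under compound symmetry or a true linear slope. With person variance 0.8, residual variance 0.2 and added variance of 0.1, 0.2 or 0.4, the ratios are:

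- 0.95, 0.91, 0.86 if the added variance arises at month 6 and half of the individual response is retained at month 12
- 1.06, 1.12, 1.22 if it arises only at month 12

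**The case against.** A reader might infer that the literal model cannot be estimated at all. The parameter count does not show that. Only the split between random-effect and residual variance is unidentified; the marginal covariance is simply unstructured. With baseline as a response only, the treatment contrasts and their standard errors remain estimable, though some software may refuse the fit. The degeneracy comes from the duplicated baseline.

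A reader might also infer that a linear random slope makes the month-6 standard errors too small in its own right. Step 6 shows that this depends on the true covariance and can reverse. Nor does the protocol's interest in whether differences persist to month 12 imply that between-person variance peaks at month 6. That question concerns group means, which categorical fixed time leaves free.

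It can fairly be said that slope coding, residual covariance and fallback order commonly belong in the SAP, which is not shown. Their absence is not the point here. The protocol has itself fixed random slopes and a duplicated baseline, and that combination performs badly.

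Replacing the slopes with an unstructured matrix would not be enough either. With baseline left in both roles, the likelihood is unbounded exactly as in step 2.

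**Conclusion.** The concern holds for the model as written, through the combination of random slopes and the duplicated baseline. On the categorical reading the components are not identified and the likelihood is degenerate. On the linear reading the month-6 standard error is understated by about 9-13% for change and 17-26% for level. In the scenarios simulated at correlation 0.8, the two-contrast error rate was 8-9% for change and 12-18% for level, against a nominal 5%.

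The identification count and the unbounded likelihood follow from the specification. The sizes rest on assumed compound symmetry or AR(1), because the protocol gives no between-visit correlation, and the simulated rates also assume complete data and two-sided testing. Because the primary contrasts are affected and the remedy is cheap, the wording should be corrected before the analysis is run.

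**What to change.** 1. Delete the random slopes and specify an unstructured within-participant covariance across visits.
2. Use baseline ADAS-Cog-Plus once: either as a response level only, or as a covariate only with months 6 and 12 as responses. Under the second option the slopes must still go, since a random intercept and linear slope would have 4 parameters for 3 distinct elements. Baseline MMSE may stay as a covariate.
3. State whether the month-6 Dunnett contrast is a difference in level or in change.
4. Give a fixed fallback order for non-convergence, for example heterogeneous Toeplitz, then compound symmetry with robust standard errors.

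The cost is a sentence or two of analysis wording. An unstructured matrix over three visits has 6 parameters against 4 for the linear-slope model, which is little for 120 participants.

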### ***Primary Outcome Measure***

Our primary measure of cognitive function will be the Alzheimer's Disease Assessment Scale-Cognitive-Plus (ADAS-Cog-Plus). The ADAS-Cog-Plus score is computed using a custom script using the package 'mirt' in the statistical package R ([www.r-project.org](http://www.r-project.org)). The ADAS-Cog-Plus uses a multidimensional item response theory model to generate a global cognitive functioning score and standard error of measurement for that score from the items of the ADAS-Cog and other standard cognitive assessments. For the current study, we used the 13-item ADAS-Cog, Trail Making Test Parts A and B, Digit Span Forward and Backward, and Animal and Vegetable Fluency as the input variables into the scoring algorithm. The scoring algorithm references data from the Alzheimer's Disease Neuroimaging Initiative sample, which was composed of approximately 50% MCI cases, 25% cognitively normal individuals, and 25% dementia cases. Lower scores represent better cognitive performance; specifically, ADAS-Cog-Plus scores of approximately -1.0 indicate healthy cognitive functioning, of 0.0 indicate MCI, and of 1.0 indicate dementia.

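### The primary model uses baseline ADAS-Cog-Plus both as a response and as a covariate, so its standard errors are wrong and the Dunnett tests do not hold the overall alpha; the size depends on choices that the protocol leaves open

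*Protocol*

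**What the plan says.** All of this is in the protocol, Statistical Analyses, Primary Outcome.

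- Response and mean structure: "fixed effects of time (baseline, month 6, month 12), treatment assignment (CON, EX, Cog-Plus), and their interaction". Baseline is thus one of the modelled outcome visits.
- Covariates: "Baseline MMSE and ADAS-Cog-Plus scores will also be included as fixed effect covariates". One coefficient is implied for each score. Nothing lets it differ by visit, and nothing removes the baseline row from the response.
- Random part and estimation: "The model will include random intercepts and slopes"; "This will be done using linear mixed models using maximum likelihood estimation".
- Target: "Time will be specified as a categorical variable, thus allowing us to examine treatment differences at the primary endpoint (month 6".
- Tests: "Two planned simple contrasts will be performed using the Dunnett test", each active arm against CON. "The overall alpha will be set at 0.05".

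The outcome concerned is the ADAS-Cog-Plus, the only outcome to which alpha is allocated. The secondary complete-case analysis reuses the same model.

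**The concern.** A baseline value can be conditioned on as a covariate, or modelled as the first of the repeated responses. Used in both roles with one common coefficient, it explains itself in the baseline rows. The likelihood rewards a coefficient near 1, because the baseline residuals then almost vanish. The random effects and residual variance are shared by all visits, so that artificial precision leaks into month 6.

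At stake is the validity of the two confirmatory tests. If the month-6 standard error is too small, intervals are too narrow and the Dunnett adjustment controls a nominal rate rather than the actual one. The complete-case analysis inherits the fault and cannot reveal it.

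**Working it through.** **Inputs from the protocol.** Three visits; three arms of 34, 34 and 52; 15% attrition (34 × 0.85 ≈ 29, 52 × 0.85 ≈ 44); maximum likelihood; random intercepts and slopes; overall alpha 0.05, taken as two-sided because no side is stated.

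**Inputs not in the protocol, therefore assumed.** The correlation of ADAS-Cog-Plus between visits, the form of the random slope, and the residual structure. Variances are set to 1 at each visit unless noted.

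**The protocol's own figures.** It gives no standard error or error rate for this model beyond the alpha of 0.05. Its sample size reproduces: with a difference of 2, SD 2.85 and alpha split over two contrasts (0.025 each), n = 2 × (2.241 + 0.842)² × (2.85/2)² = 38.6, so 39 per group, with power 0.804. That calculation does not use the disputed model.

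**Step 1: residuals.** Let b be the common baseline coefficient. After removing the arm-by-visit means, the model sees

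- baseline: y0 − b·y0 = (1 − b)·y0
- month 6: y6 − b·y0
- month 12: y12 − b·y0

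The first has variance (1 − b)², which goes to zero as b goes to 1.

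**Step 2: large-sample fit.** With S(b) the covariance of these residuals, maximum likelihood chooses b and V to minimise log|V| + tr(V⁻¹S(b)). Here V is a random intercept plus a linear slope (times 0, 1, 2) plus one residual variance. For the simple month-6 contrast the arm sizes cancel, so

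R = model SE / true SE = √[V66 / Var(y6 − b·y0)], and per-comparison error = 2Φ(−1.96·R).

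Example, equal correlation 0.7: b = 0.887. True variance = 1 + 0.887² − 2 × 0.887 × 0.7 = 0.545. Fitted V66 = 0.302. R = √(0.302/0.545) = 0.744. Error = 2Φ(−1.459) = 14.5%.

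| Assumed correlation | b | true variance | fitted V66 | R | error | interaction: R, error |
|---|---|---|---|---|---|---|
| equal, 0.5 | 0.796 | 0.838 | 0.468 | 0.747 | 14.3% | 0.875, 8.6% |
| equal, 0.7 | 0.887 | 0.545 | 0.302 | 0.744 | 14.5% | 0.875, 8.6% |
| equal, 0.9 | 0.965 | 0.194 | 0.107 | 0.743 | 14.6% | 0.874, 8.7% |
| AR(1), 0.6 | 0.885 | 0.721 | 0.454 | 0.794 | 12.0% | 0.902, 7.7% |
| AR(1), 0.9 | 0.984 | 0.197 | 0.135 | 0.828 | 10.4% | 0.913, 7.4% |

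Data with true random slopes give an SE 20%–25% too small and an error of 11.7%–14.1%. Unstructured covariances give 22%–24% and 12.5%–13.7%.

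**Step 3: interaction contrast.** If the effect is read as change from baseline, (y6 − b·y0) − (y0 − b·y0) = y6 − y0. With complete data the covariate cancels and gives no adjustment. Over all the structures tried, the SE is still 9%–17% too small in large samples, with an error of 7.4%–10.2%.

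**Step 4: finite-sample simulation under no effect**, 1000 trials per setting, linear random slope, simple month-6 contrast.

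- 29/29/44 evaluable, baseline to month-6 correlation 0.55–0.90: SE ratio 0.73–0.77, family-wise error 0.15–0.17.
- 34/34/52 with an assumed 10% missing at month 6 and 15% at month 12, equal correlation 0.5 and 0.7: SE ratio about 0.70, per-comparison error 17%, family-wise 23%. The interaction contrast gave about 12% per comparison.

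**Step 5: baseline used once.** Month-6 ANCOVA gave a family-wise error of 0.053 in the first simulation, and 6.4%–6.6% in the second, which used normal critical values.

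**The case against.** The strongest objection is that the inflation is not a necessary consequence of the text. The protocol says only that there are random intercepts and slopes, and that time is categorical. It does not say that the random slope is linear in time or that one residual variance applies to every visit.

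With random slopes on categorical time (an intercept plus month-6 and month-12 deviations, unstructured), month 6 has a variance of its own and the near-zero baseline residual does not carry over. Small simulations of that reading (29/29/44, residual SD held at 0.1, MMSE left out) gave family-wise errors of 0.08 at correlation 0.55 (200 runs) and 0.073 at 0.80 (150 runs). Monte Carlo error is about 2 points. In the limit b = 1 the contrast is a change score, with family-wise error 0.055 (20,000 runs). The cost is then mainly efficiency.

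This stands as a limit on the size, not as a defence of the specification. That model has 6 random-effect parameters plus a residual variance, 7 in all, for a 3 × 3 covariance with only 6 free elements. Its likelihood degenerates as the residual goes to zero, and software may warn or refuse.

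It can also be said that the interaction will be tested. The protocol plans simple contrasts of arm differences at month 6, which reads more naturally as the simple difference, and the interaction is anti-conservative too under a linear slope. A random intercept alone would reduce the problem (SE 2%–18% too small, error 5.4%–10.7% for the simple contrast), but that is not the model written.

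Lastly, the trial is described as proof-of-concept. It nonetheless sets a formal alpha with multiplicity control and is sized to test significance on this outcome.

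**Conclusion.** The primary model is wrong as written. It uses baseline ADAS-Cog-Plus twice, and nothing elsewhere in the protocol undoes this. Standard errors, intervals and p-values are not valid, and the Dunnett tests do not hold the overall alpha of 0.05.

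The size is conditional. With a random intercept, a linear random slope and the simple month-6 contrast, the large-sample SE is about 17%–26% too small and the per-comparison error about 10%–15%; simulated family-wise error is about 15%–23%. With the interaction contrast the per-comparison error is about 7%–10% in large samples, and about 12% in one simulation with dropout. With random slopes on categorical time it may be near nominal. All figures rest on assumed visit correlations.

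A reader might infer more than this, in two ways. One is that the standard error is always a quarter too small and the false-positive rate always tripled. Those figures fit equal correlation with a linear slope and the simple contrast, and the protocol fixes none of these firmly enough to state them without conditions. The other is that the treatment effect is biased, or that an ineffective programme would readily pass. Under randomisation the estimate stays unbiased; what fails is the stated precision and the error rate.

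**What to change.** Use baseline ADAS-Cog-Plus once.

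- **Preferred.** Keep baseline in the response vector, constrain the three arm means to be equal at baseline (constrained longitudinal model), and delete ADAS-Cog-Plus from the covariates. Every randomised participant with a baseline value stays in the likelihood, in line with the intention-to-treat commitment.
- **Alternative.** Take months 6 and 12 as the only responses, with baseline ADAS-Cog-Plus and its interaction with time as covariates. Participants with no follow-up value then drop out of the likelihood, and the text should say so.

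In either case, state the covariance structure across visits and define the two Dunnett contrasts explicitly at month 6. Make the same change in the complete-case analysis, which reuses this model. The cost is about one sentence in the protocol and its counterpart in any analysis plan, with no new data.
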